#### Cost-effectiveness outcomes

A health economic evaluation will be conducted according to international guidelines [45, 46]. All clinical and cost data will be collected alongside the trial. A health sector perspective will be applied to estimate cost utility using the EuroQol Health Outcome EQ-5D-5L instrument and the Danish quality-adjusted life-year (QALY) weights to calculate gained QALYs within a 1-year horizon [47, 48]. For the estimation of patient-specific costs, we will apply the unique Danish civil registration number for each participant to combine registrations of all healthcare consumption from 1 year before enrolment to 1-year follow-up. Data will be taken from the National Patient Register, the National Health Insurance Register, and the Danish National Prescription Registry. Productivity costs will be estimated in a separate analysis measured by a self-developed questionnaire with questions regarding days of sick leave and level of productivity. Patients’ co-payments and other condition-related expenses will also be estimated by using questionnaires during all follow-ups.

### Adverse events

Participants will be asked to report any adverse events to the physiotherapists immediately after they occur by either telephone, text message or e-mail. Expected adverse events due to the injection are plantar fascia rupture, signs of infection (e.g., fever and local swelling and redness), and local pain in the area of injection lasting more than 48 h after injection. Adverse events after the palpation-guided injection are rare, and two trials that used ultrasound-guided injections reported that no adverse events occurred [19–21]. No stopping rules are planned. Expected adverse events due to the exercise are injuries to the musculoskeletal system, such as muscle tears, muscle strains, a sprained joint, injury from falling or exacerbation of symptoms related to PF, delayed-onset muscle soreness equal to or greater than 20 mm on a 0 to 100-mm VAS that lasts for more than 48 h after performing the exercises, or exacerbation of PF.

Adverse events will be graded 1 to 5 according to the Common Terminology Criteria for Adverse Events v4.03 [49]. A medical doctor specialised in either rheumatology or general medicine will assess and grade the adverse event and ultimately make the decision whether the participant should be withdrawn from the trial due to the adverse event. If the adverse event is a grade 1 (mild), the participant may be allowed to skip one or two training sessions without any assessment. If the adverse event recurs after having skipped the exercise, the participant will have to be assessed by the medical doctor before participation in the trial is continued. If a participant experiences an adverse event and requests withdrawal from the study, data until the last exercise activity before the adverse event occurred will be included in the analyses. The physiotherapists will report any incidents to the sponsor as quickly as possible and no later than 15 days after the participant reported the event. The sponsor will report any severe adverse events (grade 3–5) to the Ethics Committee of North Denmark Region no later than 7 days after being informed. All adverse events will be reported in the future reporting of the trial. Any participants who experience harm from trial participation will receive compensation by the Patient Compensation Association.

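### The only adverse event collection described is self-initiated report by unblinded participants, so harms may be under-captured and unequally ascertained between arms

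*Protocol article*

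**What the plan says.** All references are to the protocol article.

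- **Collection.** The Adverse events section states: "Participants will be asked to report any adverse events to the physiotherapists immediately after they occur". It then fixes the grading scale, the assessor and the deadlines for onward reporting. It mentions no scheduled question, checklist or diary item.
- **Expected events.** These are listed by intervention: "Expected adverse events due to the injection are plantar fascia rupture, signs of infection" and, for PAX and PAXI, "Expected adverse events due to the exercise are injuries to the musculoskeletal system". Worsening of plantar fasciopathy (PF) appears only in the exercise list. Nothing is listed for advice and heel cup.
- **After a mild event.** For grade 1, "the participant may be allowed to skip one or two training sessions without any assessment". If the event recurs, a doctor must assess the participant before participation continues.
- **Common to all arms.** "All adverse events will be reported in the future reporting of the trial". Compensation is also general: "Any participants who experience harm from trial participation will receive compensation by the Patient Compensation Association".
- **Scheduled contact.** Every arm has a physiotherapist contact two weeks after inclusion, a hospital visit at 12 weeks, and e-mailed questionnaires at 4, 26 and 52 weeks (Design and setting; Patient advice and heel cup). The follow-ups already carry additional items: co-payments and expenses "will also be estimated by using questionnaires during all follow-ups" (Cost-effectiveness outcomes).

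**The concern.** A count of spontaneous reports depends on how often events occur and on how readily participants get in touch. In this trial the second factor could differ by arm. Participants cannot be blinded to exercise or to an injection, and the Limitations section confirms that PAX receives no placebo injection. The recipients of the reports are the treating physiotherapists (Roles and responsibilities). PAXI participants have had an invasive procedure, exercise participants have a programme to ask about, and PA participants have neither.

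Harms also bear on the conclusion. The Strengths section says that if no arm proves superior, the choice should fall on the least invasive or most cost-effective option, subject to patient preference. Readers will then set the adverse event counts of the three arms side by side, whether or not a formal test is planned.

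**Working it through.** **1. The plan's own figures.** The document gives no adverse event rate, no capture rate and no power for harms, so there is no figure to reproduce. The one usable design number is 180/3 = 60 participants per arm (Sample size).

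**2. The sections side by side.**

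- *PASS (Secondary outcomes):* participants report it when it occurs and are also asked about it at follow-up. Here the authors state the scheduled question.
- *Adverse events:* participants report when events occur. No scheduled question follows.
- *Project diary (Patient advice and heel cup):* treatments, self-treatment and analgesic use.
- *Orthoses and training diaries (Compliance):* heel cup use; repetitions, sets and dates. Neither records events. In particular, nothing described records the intensity and duration that define the expected muscle soreness (at least 20 mm for more than 48 h).
- *Two-week contact:* invites the participant's own questions about the condition, taking part and the exercise. Adverse events are not named.
- *Deterioration of PF (Secondary analyses):* a fall of at least 14.1 points in FHSQ pain between follow-ups, or loss of PASS. It comes from scheduled data in all arms and is compared by risk difference. It does not cover fascia rupture, infection, strains or falls.

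**3. Timing after the injection.** The injection may be given up to 14 days after baseline. Prolonged local pain is defined as lasting more than 48 h. If inclusion and baseline are the same day (assumption) and the contact falls on day 14, the 48 h have passed only for injections given by day 14 − 2 = 12. The contact therefore cannot be relied on to pick up post-injection events, even if it were used for that purpose.

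**4. Possible size.** Let *p* be the true risk, equal in all arms, and *c* the share of affected participants whose event reaches the trial.

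- Reported risk = *p* × *c*
- False risk difference = *p* × (*c*₁ − *c*₂)
- False risk ratio = *c*₁ / *c*₂

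Assumed ranges, none from the document: *p* = 10–30%, *c*₁ = 80–90%, *c*₂ = 40–60%.

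- Smallest difference: 0.10 × (0.80 − 0.60) = 0.02
- Largest difference: 0.30 × (0.90 − 0.40) = 0.15
- Risk ratio: from 0.80/0.60 = 1.33 to 0.90/0.40 = 2.25, where the truth is 1
- Example, *p* = 20%, capture 90% and 60%: reported 0.18 and 0.12, or 10.8 and 7.2 of 60; difference 6 points, ratio 1.5
- Same example with capture reversed: difference −6 points, ratio 0.12/0.18 = 0.67
- Equal capture at any level: difference 0, ratio 1. At 75% in both arms, 0.20 × 0.75 = 0.15 is reported in each, so the absolute rate is still too low

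**5. Direction.** The rule on skipping sessions can apply only to exercise arms and might prompt a call. The required medical assessment on recurrence might discourage one. Exercise participants are also told to expect pain, with no ceiling if it is tolerable (Heavy-slow resistance training), which could make them regard an event as not worth reporting. These forces pull in opposite directions, and the document gives no means of weighing them.

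**The case against.** The strongest reply is that the article condenses a full protocol (version 2.0, not shown) and that the SPIRIT schedule figure is unavailable, so a scheduled adverse event question may exist. This stands, and it makes the fix conditional. It does not remove the point: the section sets out its procedure in some detail, and the same article mentions the scheduled question where PASS has one.

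A reader might infer more than the text supports:

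- *That spontaneous report is stated to be the sole route.* The article describes one route and excludes no other.
- *That collection is limited to the active arms.* The request covers any adverse event in any participant. Listing expected events by intervention is ordinary practice, and the list is not said to be given to participants as a prompt.
- *That exercise participants are rewarded for reporting.* The session rule is a management rule and is offset by the assessment requirement. The one explicit benefit, compensation, is open to everyone.
- *That harms cannot be compared fairly.* The article states no between-arm test of adverse events, and PF deterioration is measured alike in every arm.

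The 12-week visit and the registers of healthcare use may also bring to light events that led to care, although neither is described as a source of adverse events. Finally, a mid-trial change mixes two collection methods over time. That is true, but allocation is 1:1:1 in small blocks, so the change would fall on the three arms about equally.

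**Conclusion.** The concern holds as a weakness in the described method. The article does not demonstrate a bias. Self-initiated report by unblinded participants to the treating physiotherapists is the only collection route it sets out, and PF exacerbation is named as an expected event for exercise alone. Adverse events may be under-captured and unequally ascertained, with the direction unknown.

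The size rests wholly on unknown capture rates. Under the assumed ranges the false difference is 2 to 15 percentage points in either direction; it is zero if capture is equal. The primary analysis of FHSQ pain is unaffected. What is at risk is the harms table and any choice between arms that leans on it. The conclusion also assumes that the full protocol contains no scheduled adverse event question; if it does, one clarifying sentence is enough.

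**What to change.** State whether adverse events are asked about at follow-up. If they are not:

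1. Add identical short items to the 4-, 12-, 26- and 52-week follow-ups in all three arms: the expected events already listed, including PF exacerbation, plus one open item, each covering the period since the last follow-up.
2. Base any between-arm description of harms on these solicited answers, with the number asked and the number answering in each arm.
3. List spontaneous reports separately, by arm and grade.

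None of this changes a clinical management rule.

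**Cost.** A few extra items in follow-ups that already take place. Follow-ups already completed would have no solicited data: 96 of 180 participants were included at submission, leaving 180 − 96 = 84 to come. From first inclusion (7 February 2019) to submission (5 October 2019) is 240 days, about 34 weeks, so no participant had yet reached week 52. The report should give the date of the change and the numbers asked before and after it. Solicited items give each arm the same opportunity to report. They do not blind participants, and recall over the later 26-week interval will be imperfect, so some caution in interpretation remains.

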### Interventions

#### Patient advice and heel cup

Participants in all three groups will receive the same initial fundamental patient advice and leaflet about their condition before randomisation. They receive brief information about pathology, risk factors and advice on how to decrease activities that lead to symptom flares and slowly progress back to former activity levels guided by symptoms. To ensure that all participants receive the exact same information, the physiotherapists read a written information out loud; however, they will ask control questions to clarify if the participants understand the information and allow participants to pose questions about the information and participation in general. The leaflet includes the same information that the physiotherapists deliver orally after inclusion in the trial.

Participants will be asked to refrain from seeking other treatments during the course of the trial. They will be allowed to self-treat their PF for pain relief (e.g., with ice or heat packs, rolling a tennis ball under the heel, or massaging the plantar fascia) if they have been doing this for at least 4 weeks prior to inclusion, but they will not be encouraged to do so. Participants will be handed a project diary in which they are asked to record any treatment that they may have received during the course of the trial, including any type of self-treatment and use of analgesic or anti-inflammatory substances. We will inform participants that follow-up on outcomes is critical, regardless of whether they comply with their allocated treatment. Two weeks after inclusion, the physiotherapist who included the participant will contact the participant to ask if they have any questions regarding the condition, the practicalities of participation, or in relation to performing the exercise depending on randomisation. If participants have not achieved a self-evaluated satisfactory result after 12 weeks, they may discuss other evidence-based treatments (e.g., plantar fascia stretching) with the physiotherapist, but they will be encouraged to continue to comply with their allocated treatment.

We will give all participants a silicone heel cup (Medi-Dyne Healthcare Products, Colleyville, TX, USA) for each shoe, and they are advised to use the heel cups whenever they are wearing shoes. If participants already use an insole or another type of foot orthosis, they are allowed to continue wearing this if they prefer this over the heel cups.

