#### Heavy-slow resistance training

Participants of the PAX and PAXI groups will be instructed in performing a heel-raise exercise standing with the forefoot on a step or a book as per Rathleff et al. [26]. Unlike the pre-determined programme used in that trial, we will use a self-dosed programme that we recently found to be associated with the same level of improvement as the pre-determined programme [16]. Participants will be told that it is important that the exercise be performed with an adequately heavy load, and they will be instructed in performing the heel raise with a load corresponding to an 8 repetition maximum (RM) (i.e., a weight that can only be lifted eight times). They may only use a lower relative load if they feel they are unable to perform the exercise with 8 RM. They shall perform the exercise for as many sets as possible. The exercise descriptors are elaborated in Table 1. If participants feel they are able to perform more than eight repetitions with only their body mass (8 RM), an external load consisting of a backpack with books, weights or water bottles to add weight must be used. We will tell participants that pain during the exercise is expected and that there is no upper limit of pain they are allowed to experience, as long as they feel it is tolerable. Participants randomised to also receive the injection will be asked not to perform the exercise within 24 h from the injection and not to progress the method used to achieve 8 RM until 2 weeks after the injection. If heel raise without a backpack is sufficient to achieve 8 RM before the injection, participants should not perform the exercise with a backpack until the third week after the injection, regardless of any pain reduction following the injection. They will be told to perform the exercise until they achieve their Patient Acceptable Symptom State (PASS) (please see ‘Secondary outcomes’ section for elaboration) and an additional 4 weeks. To support the exercise execution, participants receive a written exercise instruction that also includes pictures of the exercise (Fig. 1).

**Table 1 Tab1:** Exercise descriptors

1. Load magnitude	8 repetition maximum
2. Number of repetitions	≥ 8 depending on the load
3. Number of sets	As many as possible
4. Rest between sets	2 min
5. Number of exercise interventions	Every other day
6. Duration of the experimental period	8 weeks

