### Statistical analyses

All statistical analyses will be performed by a blinded data analyst according to a pre-established analysis plan using the intention-to-treat principle. This plan is written in consultation with a statistician and will be published on the Aalborg University website before the inclusion of the last participant. SPSS software (IBM Corporation, Armonk, NY, USA) will be used as statistical software. We will use Q-Q plots and histograms to assess data normality. Missing outcome data will be imputed using multiple imputations based on the values from previous follow-ups, sex, age, and group allocation.

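### For participants who withdraw after an adverse event, the protocol cuts the analysed data at the last exercise session; this conflicts with intention-to-treat and cannot be applied in PA, though its effect is probably small

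*Protocol article*

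**What the plan says.** The rule stands in the protocol article under Adverse events. Its trigger has two parts: "If a participant experiences an adverse event and requests withdrawal from the study". Its consequence is that "data until the last exercise activity before the adverse event occurred will be included in the analyses". No other data rule for such participants is given, and none is given for the PA arm.

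Four other statements bear on it:

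- Statistical analyses: the analyses will be done "according to a pre-established analysis plan using the intention-to-treat principle".
- Statistical analyses: "Missing outcome data will be imputed using multiple imputations". The listed predictors are earlier scores, sex, age and arm. Adverse events are not among them.
- Heavy-slow resistance training: "Participants of the PAX and PAXI groups will be instructed in performing a heel-raise exercise". PA receives advice and a heel cup only.
- Adverse events: the expected harms of exercise include "injury from falling or exacerbation of symptoms related to PF".

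**The concern.** The cut-off is a treatment event that comes before the harm. It is not the date on which consent ends. A questionnaire completed with consent after the last session before the event, but before the withdrawal request, is left out by plain implication. An analysis by intention-to-treat would keep it.

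Two features make this more than untidy wording. First, the rule refers to something that exists in only two of the three arms, so the arms cannot be handled alike. Second, a flare of the heel condition counts as an adverse event, so the excluded score may record the very worsening that FHSQ pain measures. The same scores feed the secondary deterioration outcome, defined by a fall of at least 14.1 points. Imputation from earlier scores and arm would then fill the gap as though no event had happened. If so, the comparisons of PAX and PAXI with PA (Hypotheses 2 and 3) could lean towards exercise.

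**Working it through.** **Inputs from the protocol article.** Target difference 14.1 points, SD 22, two-sided 5%, power 90%, 53 per group raised to 60 (Sample size). Outcome visits at 4, 12, 26 and 52 weeks; conclusions at 12 weeks only (Primary analysis). Exercise every other day (Table 1). The documents give no adverse-event rate, withdrawal rate or post-event score, so these are assumptions below.

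**1. The plan's own figure.** The normal approximation gives n = 2 × (1.960 + 1.282)² × 22² / 14.1² = 51.2, rounded up to 52. The two-sample t-test gives 52.14, rounded up to 53, with power 90.5% at 53 and 93.6% at 60. The stated 53 reproduces, and this point does not change it.

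**2. What the rule removes.** Scores after the withdrawal request would not normally exist under any rule. The rule itself removes only scores collected between the last session before the event and that request. The 12-week score can fall there in two ways:

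- The event and the request fall on either side of the 12-week visit.
- Exercise ended before week 12, and a later event with a request sends the cut-off back past a completed 12-week score. Table 1 gives 8 weeks for the experimental period, and the text ends exercise 4 weeks after PASS. By that second criterion exercise stops before week 12 only if PASS comes before week 8. The Background says that only 6% reached an acceptable state within 12 weeks of such training (0.06 × 60 = 3.6 per arm).

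**3. Formula.** Shift in an exercise-arm mean = (participants whose 12-week score is removed / 60) × (points by which their true score lies below the imputed one). A simulation checked this, with 60 per arm, correlation 0.5 between visits, and deletion followed by regression imputation within the arm. With 5% of the arm affected (3 of 60 on average) and a gap of 14.1, the formula gives 0.71 and the simulation 0.72. With 10% and a gap of 22, both give 2.2.

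**4. Ceiling, if every 12-week score of these participants were lost through the rule.** Assume 3 to 6 of 60 and a gap of 10 to 20 points.

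- 3/60 × 10 = 0.5 points
- 6/60 × 20 = 2.0 points, and 2.0/14.1 = 14%

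**5. Loss attributable to the rule.** Assume events spread evenly over 12 weeks and a window of 1 to 2 weeks from last session to request. The 12-week visit then falls in the window for 1/12 to 2/12 of those participants.

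- Low: 3 × 1/12 = 0.25 participants; 0.25/60 × 10 = 0.04 points (0.3% of 14.1)
- High: 6 × 2/12 = 1.0 participant; 1.0/60 × 20 = 0.33 points (2.4% of 14.1)

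The text sets no limit on the time between event and request. A 4-week window doubles the high case to 2/60 × 20 = 0.67 points. One further participant lost by the late route changes the arm mean by 10/60 = 0.17 to 20/60 = 0.33 points. There the 12-week score may predate the event and need not be poor, so the direction is open.

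**6. Set against precision.** At 60 per group the standard error of a difference is 22 × √(2/60) = 4.02 and the 95% half-width is 1.96 × 4.02 = 7.9 points. With no true difference, a shift of 0.33 raises the chance of a finding in favour of exercise from 2.5% to Φ(−1.96 + 0.33/4.02) = 3.0%. At 2.2 points, the largest value examined in step 3, it would be 7.9%.

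**The case against.** The strongest reply is that the rule bites on very few people. It needs both an event and a request to leave. Training is every other day and events are to be reported at once, so the window is short and visits are far apart. This stands, and it is why the ceiling in step 4 should not be read as the effect of the rule. The assumed 3 to 6 withdrawals are also generous: the whole drop-out allowance is 60 − 53 = 7 per arm, so they use 43% to 86% of it.

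A reader might see a second contradiction with the advice section, where participants are told that "follow-up on outcomes is critical, regardless of whether they comply with their allocated treatment". That sentence concerns non-compliance. Someone who stops exercising without asking to leave is not touched by the adverse-event rule. The two sit awkwardly together but do not contradict each other.

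A reader might also say that the plan hides harm. It does not: all adverse events are to be reported, and only efficacy scores are affected. Nor does the rule cover withdrawal decided by the doctor, for which the article states no data rule.

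Finally, the unseen analysis plan may settle the matter. That would be an answer if the article were silent. It states a rule, and an analyst who followed it would set aside outcome data from randomised participants.

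**Conclusion.** The sentence is wrong as written. It sets an on-treatment cut-off inside an analysis declared to be by intention-to-treat, it is undefined in PA, and it can exclude validly collected scores, including a completed 12-week score.

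The effect is probably small: about 0.04 to 0.33 FHSQ points under the assumptions in step 5, and 0.67 with the longer window. All of these are well under 1 point. They rest on assumed rates, gaps and timing.

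A reader might infer a certain bias towards exercise. The documents do not support that. It requires that scores after the event are worse than imputation predicts, and that PA data are kept in full. The first is plausible because a flare is a listed event. The second is unknown, because the article does not say how a withdrawing PA participant is handled. For PAXI against PAX the rule applies to both arms, and no direction follows.

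**What to change.** Replace the sentence under Adverse events with: *All outcome data collected up to withdrawal of consent are analysed in the randomised group, in every arm.* Add: *Stopping the allocated treatment after an adverse event does not by itself end the scheduled outcome questionnaires.* The section then agrees with the intention-to-treat statement, and one rule serves all three arms.

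The cost is a change of wording. The sample size is unaffected and no visit is added: the questionnaires at 4, 12, 26 and 52 weeks are already scheduled, and those at 4, 26 and 52 weeks go out by e-mail. At submission 96 of 180 participants had been included, and the analysis plan was due before the last inclusion, so the same wording could be carried into that plan.
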